#### **7.4.4 SSARs (Suspected Serious Adverse Reactions)**

Suspected Serious Adverse Reactions are adverse reactions (or events) that are thought to be related to the research procedure. For the purpose of this trial the following is a list of potential SSARs:

- Fibrosis
- Delayed wound healing
- Wound infection
- Wound breakdown
- Haematoma in breast or axilla
- Seroma
- Dermatitis associated with radiation
- Telangiectasia
- Pain in irradiated field
- Oedema

SSARs should be reported as described in 7.4.2

#### **7.4.5 SUSARs (Suspected Unexpected Serious Adverse Reactions)**

Suspected Unexpected Serious Adverse Reactions are adverse reactions (or events) that are thought to be related to the research procedure but do not appear on the list in 7.4.4. SUSARs should be reported as described in 7.4.2, but certainly, within 24 hours.

### **7.5 Deaths**

All deaths, with date and cause, must be reported as soon as possible to the TARGIT Trial Operations Office on the appropriate CRF. Deaths which also meet the SAE criteria should additionally be reported as described in 7.4.2.

### **7.6 Withdrawal of Consent**

Patients may “opt out” of the trial at any time. Rarely, patients may also wish to withdraw consent for further data collection. Such cases should be reported to the TARGIT Trial Operations Office so that no further data are entered onto the database.

## SECTION 8

### DATA OWNERSHIP AND PUBLICATION

The management of this trial is the responsibility of the International Steering Committee (ISC), which also owns the rights to the overall data of the trial. Individual centres own the rights to the data collected on patients entered from their own centre but by agreeing to participate in the International TARGIT Trial investigators also agree not to present or publish any analysis of the data on trial patients according to the randomised allocation until after the first publication of the overall result for the whole trial. The 'Policy for Publication of the Trial', as agreed by the International Steering Committee, is given in a separate document.

The ISC will meet regularly and review all matters of trial conduct and will also address any questions raised relating to the trial. Although Carl Zeiss Inc will be represented on the ISC, the prime responsibility for any decisions on the management of the trial will lay with the clinical and scientific academic members of the Committee.

#### 8.1 Trial Administration

Since this trial is an international multi-centre trial it has been agreed that each centre takes responsibility for the collection and management of its own data. Randomisation can be performed centrally through the TARGIT Trial Operations Office or may be carried out locally provided the centre agrees to and abides by the 'Standard Operating Procedures for Randomisation' (available as a separate document). Several centres (e.g., in a defined geographical location) may wish to collaborate together for the randomisation process and for data collection. This is acceptable provided the arrangement is agreed by the ISC.

Definition of the data set may be determined locally provided that it accommodates the overall trial dataset as defined in the 'Data Collection Standard Operating Procedures'. Data may either be held locally and downloaded to the TARGIT Trial Operations Office as required (or at least every six months) or added directly to the trial's database via a secure website. Other methods of data entry include email, fax, and post. Each centre will be allowed only to access data on their own patients from this website. Only certain members of the ISC, the Trial Statistician and the International Project Co-ordinators will be able to access all the data. Regular electronic reports will be produced and passed to each centre for audit and checking purposes. This is a new way of managing an international clinical trial but one which allows each centre to have full responsibility for its own data.

The ISC will discuss with each centre the safeguards that are in place to secure and protect the data at their centre and also to ensure that the randomisation codes are correctly generated, stored and used for the allocation of treatments to individual patients. Failure to comply with the standards agreed by the ISC will result in all data from that centre being removed from the trial analysis.

Any data management or clinical queries should be addressed in the first instance to the Principle Investigator at the local centre. If he/she cannot adequately address the question it should be passed to the TARGIT Trial Operations Office which will either deal with the query directly or will pass it on to the co-chairs of the International Steering Committee or an agreed expert.

## SECTION 9

### STATISTICAL CONSIDERATIONS

#### 9.1 Patient Numbers and Power Calculations

The objective of the trial is to determine whether the use of intra-operative radiotherapy gives equivalent rates of local control to those obtained using external beam treatment.

This is a Non-Inferiority Trial – One Sided design and we have selected a clinically meaningful non-inferiority margin  $\delta_0 > 0$ . We are interested in testing  $H_0: \delta = \delta_0$  versus  $H_1: \delta < \delta_0$  using a one-sided level- $\alpha$  test with power  $1 - \beta$  to reject  $H_0$  when  $\delta = 0$ .

We have defined the power calculations for this trial using absolute values for local breast relapse. Estimates have been obtained from published data. The CRC Trial compared the outcome of patients with good prognosis early breast cancer who had undergone breast conserving surgery and randomised to post-operative radiotherapy, demonstrated a local recurrence rate of 9% at five years in the arm treated with conventional radiotherapy. The World Overview of radiotherapy in breast cancer showed a baseline rate of about 7.8% at about 10 years. However most of these trials were started in or before 1985 and the techniques of giving radiotherapy have much improved since then such that many papers are reporting much lower rates with conventional radiotherapy.

With a baseline relapse rate of 6 % at 5 years and allowing an absolute increase or decrease in relapse rate of 2.5% (the non-inferiority margin) with 1116 patients randomised to each treatment will give a power of 80% (see Table). Thus if the recurrence rate in the IORT arm is greater than 8.5% (or lower than 3.5%) there will be an 80% chance of demonstrating a difference. If the absolute rate of recurrence is lower e.g. 5% we would have about an 85% chance of detecting a difference. This trial therefore requires a total of 2232 patients to have adequate power to meet the primary objective.

|                      | Relapse rate | Power      |            |             |             |             | Confidence Interval      |       |
|----------------------|--------------|------------|------------|-------------|-------------|-------------|--------------------------|-------|
|                      |              | 60%        | 70%        | 80%         | 90%         | 95%         | Lower                    | Upper |
| PA | 0.03         | 336        | 438        | 576         | 797         | 1008        | ( 0.005 , 0.055 )        |       |
|                      | 0.04         | 443        | 578        | 760         | 1052        | 1330        | ( 0.015 , 0.065 )        |       |
|                      | 0.05         | 548        | 715        | 940         | 1302        | 1645        | ( 0.025 , 0.075 )        |       |
|                      | 0.06  | 650 | 849 | 1116 | 1546 | 1953 | ( 0.035 , 0.085 ) |       |
|                      | 0.07         | 751        | 980        | 1288        | 1784        | 2254        | ( 0.045 , 0.095 )        |       |
|                      | 0.08         | 849        | 1108       | 1456        | 2017        | 2549        | ( 0.056 , 0.105 )        |       |
|                      | 0.09         | 944        | 1233       | 1620        | 2244        | 2836        | ( 0.067 , 0.115 )        |       |

"Statistical Methods in Medical Research" 3rd Edition p.201  
P. Armitage & G.Berry, Blackwell Scientific Publications 1994

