### 9.4 Statistical Analysis

The major endpoint is the incidence of local recurrence. This will be compared on the basis of 'intention to treat' (i.e. all randomised patients will be analysed) and the logrank test will be used. This will be performed once the baseline data have been compared to test the randomisation and to define whether any stratified analyses are required. In addition ratios of radiological lesion size to clinical and pathological size, and of specimen weight will be compared to ensure that the extent of the surgical procedure was similar in both groups. The baseline comparisons between the two groups will be done using chi-squared test for categorical variables and independent two sample t-test for all continuous variables. Statistical significance will be defined at the  $p < 0.05$  level. We will use Kaplan-Meier curves and proportional hazard regression models to account for time-to event and censoring of the data.

In addition, exploratory subgroup analyses will be performed on the main endpoint including variables such as tumour size, grade and axillary nodal involvement. These will be stipulated in the Statistical Analysis Plan agreed by the International Steering Committee before any analysis is undertaken.

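### Protocol 9.1 presents its 80% non-inferiority power as the chance of demonstrating a difference at 8.5% v 6%; at 1,116 per arm that chance is about 63% (two-sided 0.05) or 74% (one-sided 0.05)

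*Combined protocol and SAP*

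**What the plan says.** Protocol 9.1 declares the design: "This is a Non-Inferiority Trial – One Sided design". The null hypothesis is that the difference equals the margin, and power is defined as the chance of rejecting that null when the true difference is zero, that is, when the arms are equal. The planning inputs follow. The control rate is introduced by "With a baseline relapse rate of 6 % at 5 years". The margin is 2.5 percentage points, described as applying to a rise or a fall. The sample size is 1,116 per arm, for 80% power. Alpha appears only as a symbol.

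The next two sentences interpret the result. The first, on the chance of demonstrating a difference, reads "Thus if the recurrence rate in the IORT arm is greater than 8.5% (or lower than 3.5%) there will be an 80% chance". The second says that, if the rate is lower, for example 5%, "we would have about an 85% chance of detecting a difference".

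Protocol 9.4 compares local recurrence by intention to treat ("i.e. all randomised patients will be analysed) and the logrank test will be used"), at p < 0.05 with no sidedness given. It mentions neither the margin nor a confidence limit. Protocol 9.2 later raises accrual to 3,432 and gives no revised power. SAP 8.2 tests non-inferiority by the difference in binomial proportions at 5 years with a 90% confidence interval, and excludes the log-rank, Kaplan-Meier and proportional hazards methods from that purpose.

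**The concern.** Power to show non-inferiority when the arms are equal and power to detect a difference when they are not are computed under different true states. Protocol 9.1 defines the first and then describes it as the second. Under its own test, a true IORT rate of 8.5% against 6% lies exactly on the null boundary. The chance of rejecting the null there is the type I error, not 80%.

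This matters because protocol 9.4, read alone, makes a log-rank test of difference the main comparison. A reader who believes that the trial had 80% power to see an excess at the margin would be more reassured by a non-significant log-rank result than the design allows.

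**Working it through.** **Inputs.** From protocol 9.1: baseline rate 6%, margin 0.025, 1,116 per arm, stated powers 80% and about 85%. From protocol 9.4: log-rank, p < 0.05. Two-sided is assumed because the sentence looks in both directions; one-sided is shown as well. From protocol 9.2: revised total 3,432, taken as 1,716 per arm on the assumption of an equal split.

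**Reproducing the plan's figures.** With true rates equal at p,

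n = 2p(1−p)(z₁₋α + z₁₋β)² / margin².

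At p = 0.06, one-sided alpha 0.05 and power 80%:

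n = 0.1128 × (1.645 + 0.842)² / 0.000625 ≈ 1,116.

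The same formula reproduces all 35 cells of the 9.1 table to within one patient. One-sided 0.025 gives 1,417 and does not fit. One-sided 0.05 also agrees with the 90% interval in SAP 8.2.

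Non-inferiority power at 1,116 per arm:

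- 6% v 6%: Φ(0.025/√(0.1128/1116) − 1.645) = 80.0%
- 5% v 5%: Φ(0.025/√(0.095/1116) − 1.645) = 85.7%

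These are the protocol's 80% and about 85%. At a true 8.5% v 6% the same test rejects its null with probability Φ(0 − 1.645) = 5%.

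**Power to detect a difference.** SE = √{[p₁(1−p₁) + p₂(1−p₂)]/1116}; power = Φ(0.025/SE − z), with z = 1.960 (two-sided 0.05) or 1.645 (one-sided 0.05).

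| True rates | SE | 0.025/SE | Two-sided | One-sided | Protocol 9.1 |
|---|---|---|---|---|---|
| 8.5% v 6% | 0.01096 | 2.280 | 62.6% | 73.7% | 80% |
| 3.5% v 6% | 0.00899 | 2.781 | 79.4% | 87.2% | 80% |
| 7.5% v 5% | 0.01023 | 2.443 | 68.5% | 78.8% | about 85% |
| 2.5% v 5% | 0.00803 | 3.115 | 87.6% | 92.9% | about 85% |

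The protocol does not name the contrast behind its 85%, so both directions are shown.

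**Checks on 8.5% v 6%, two-sided.** A pooled variance gives 62.5% and simulation 62.6%. For the log-rank, the hazard ratio is ln(0.915)/ln(0.94) = 1.436 and the expected events are 1116 × (0.06 + 0.085) ≈ 162, giving 63.3% (74.4% one-sided). An 80% figure for this contrast appears only if the 6% variance is used in both arms with one-sided 0.05, which understates the variance at 8.5%.

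**Numbers needed for 80% power, 8.5% v 6%.** Two-sided 0.05: (1.960 + 0.842)² × (0.0564 + 0.0778)/0.000625 ≈ 1,685 per arm. One-sided 0.05: about 1,330.

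**At the revised total.** SE = √[(0.0564 + 0.0778)/1716] = 0.00884; Φ(0.025/0.00884 − 1.960) ≈ 81% two-sided for 8.5% v 6%.

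**The case against.** The strongest reply is that no design number is wrong. The hypotheses and the definition of power stand correctly in the same section, the table reproduces, and 80% and about 85% are right as non-inferiority power. That stands. A reader might infer from the faulty sentences that 1,116 per arm was too few for the primary objective; the documents do not support this. The figures near 1,685 and 1,330 belong to a different objective.

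A reader might also infer that the trial would miss about 37% of true excesses at the margin. That holds only for 1,116 per arm, a 6% baseline, a true rate of exactly 8.5% and a two-sided 5% test. The sentence says greater than 8.5%, and power rises from there. At 3,432 patients the figure is about 81%. Protocol 9.2 also reports far lower early recurrence than expected (0.3% at two years). With 1,116 per arm, two-sided power for a 2.5-point increase would be 91.6%, 83.5% or 75.6% from assumed baselines of 2%, 3% or 4%.

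Nor would the plan as a whole accept a null log-rank as proof of non-inferiority: SAP 8.2 already rules that out. What remains is that protocol 9.4 does not say so.

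Finally, none of these detection figures describes the analysis now planned. The SAP uses p < 0.001 for local recurrence and reports each stratum separately. At two-sided 0.001, power for 8.5% v 6% with 1,116 per arm is about 16%. This is a reason to label any quoted detection power carefully. It does not make the 9.1 sentences correct.

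**Conclusion.** The two interpreting sentences in protocol 9.1 are wrong as written. On the 8.5% side, the stated 80% exceeds the actual detection power by about 17 points at two-sided 0.05 or 6 points at one-sided 0.05. For 7.5% v 5%, the stated 85% exceeds it by about 16 or 6 points. On the 3.5% side, two-sided power of about 79% makes the claim nearly right, but by coincidence. The choice between 63% and 74% depends on sidedness, which protocol 9.4 leaves open; both fall short of 80%. The sample size, the table and the non-inferiority power are sound. The figures assume 5-year binomial proportions with no allowance for dropout, since 9.1 states none; the log-rank approximation agrees within about one point.

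**What to change.** In protocol 9.1, replace the two sentences with wording such as: *With 1,116 patients per arm and true 5-year rates of 6% in both arms, there is 80% power (about 86% if both rates are 5%) for the upper one-sided 95% confidence limit of the IORT minus EBRT difference to fall below 2.5 percentage points.* State the one-sided alpha of 0.05. Remove the words about a decrease from the margin, which in a one-sided design applies only to an increase.

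If detection power is quoted as well, give its sidedness and sample size. For 8.5% v 6%: about 63% two-sided or 74% one-sided at 1,116 per arm, and about 81% two-sided at 3,432 in total (equal split and whole-trial analysis at p < 0.05 assumed). For 3.5% v 6%: about 79% two-sided at 1,116 per arm.

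In protocol 9.4, state the sidedness of p < 0.05 and carry over the SAP 8.2 rule that the log-rank and related methods do not test non-inferiority.

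The cost is wording only. No sample size, margin, test or data collection changes, but the stated chance of detecting an excess becomes less favourable.

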#### 9.2 Revision of Patient Numbers

On 24 March 2010 the International Steering Committee and Data Monitoring Committee reviewed the results of an interim analysis. This showed an overall lower than expected recurrence rate at two years of 0.3% (95% CI 0.08-1.2, Kaplan-Meier estimate). A decision was made to increase accrual by an additional 1200 patients to 3432. This will also enable accrual into the sub-protocols.

### 9.3 Early Stopping

The DMC would keep under review the full range of adverse event data being collected and draw conclusions on safety by considering all events. If however any of the following were demonstrated at  $p < 0.01$  they would consider recommending early stopping:

- A significant increase in grade 4 skin or rib fractures (as a sign of radionecrosis)
- Delays in wound healing which after detailed review by the DMC as to time course and severity were considered clinically significant.

Early stopping could be applied on specific strata, while other strata are allowed to continue recruitment.

### 9.4 Statistical Analysis

The major endpoint is the incidence of local recurrence. This will be compared on the basis of 'intention to treat' (i.e. all randomised patients will be analysed) and the logrank test will be used. This will be performed once the baseline data have been compared to test the randomisation and to define whether any stratified analyses are required. In addition ratios of radiological lesion size to clinical and pathological size, and of specimen weight will be compared to ensure that the extent of the surgical procedure was similar in both groups. The baseline comparisons between the two groups will be done using chi-squared test for categorical variables and independent two sample t-test for all continuous variables. Statistical significance will be defined at the  $p < 0.05$  level. We will use Kaplan-Meier curves and proportional hazard regression models to account for time-to event and censoring of the data.

In addition, exploratory subgroup analyses will be performed on the main endpoint including variables such as tumour size, grade and axillary nodal involvement. These will be stipulated in the Statistical Analysis Plan agreed by the International Steering Committee before any analysis is undertaken.

### 9.5 Additional Sub-protocols

Additional sub-protocols will be written to address questions such as Quality of Life, Patient Preference, Health Economics, etc. Each sub-protocol will have its own statistical considerations.

Since we do not know what differences patients are willing to accept in recurrence rates in order to have a shorter treatment time we will be undertaking a patient preference study. This enables patients to make hypothetical 'trade-offs' between risk of relapse and treatment durations. Some of the investigators involved in TARGIT have already successfully used such studies to evaluate adjuvant hormone therapies. A separate sub-protocol will be available.

## **SECTION 10**

### **ETHICAL CONSIDERATIONS**

This trial, as for most randomised studies includes an experimental treatment. However, in this case the availability of the new procedure is strictly limited. There are very few machines in clinical centres and even at those centres that have the equipment, not all patients can be given the new procedure. However, should the new technique provide adequate local control and cosmesis, and be acceptable to patients it will markedly reduce the need for external beam radiotherapy for early breast cancer. This will enable a major saving of resource. The ideal time to implement a full, randomised assessment is while the technology is at fairly early stage of development. Since there are insufficient resources to give the new technique to all patients randomisation is the most ethical way to proceed. In the pilot study, every patient deemed suitable for intra-operative radiotherapy and approached consented for the procedure. We expect therefore a high acceptance of the novel arm. All suitable patients will be informed of the trial and given the opportunity to participate. Patients will be given a period (one to several days depending on the clinic timings) to consider entry and complete the consent form. Randomisation will only proceed once a signed consent form has been received at the clinic.

The trial has been planned and will be executed in line with the Declaration of Helsinki (2002).

#### **10.1 Data Monitoring Committee (DMC)**

An independent DMC has been appointed and their remit agreed. They will regularly review the data collected during the trial and report to the ISC as to whether the trial should continue and make recommendations as to changes in the protocol.

Meetings will probably be scheduled annually for the first two years of the trial whilst accrual gains momentum. More frequent meetings may then be held.

There are no formal stopping rules for the trial – these may be determined in discussion with the DMC but should a difference between the treatments in local recurrence reach  $p < 0.001$  serious consideration as to whether the trial should continue will be given.

## SECTION 11

### QUALITY ASSURANCE

Quality assurance (QA) in radiotherapy is defined as “[the set of] procedures that ensures consistency of the medical prescription and the safe fulfilment of that prescription as regards dose to the target volume, together with minimal dose to normal tissue, minimal exposure to personnel, and adequate patient monitoring aimed at determining the end result of treatment”. In the UK the Department of Health issues a mandatory standard. It is based on a formal quality management system issued by the International Standards Organisation. This is a multidisciplinary responsibility to ensure consistency in absolute dosimetry, dose delivery, volume definition and reproducibility are paramount in radiotherapy QA and have become even more important with the advent of conformal therapy. Formal procedures should ensure that every “non-conformity” (i.e., a failure of any element of the system or its procedures) is identified and controlled, and that corrective action is taken to deal with the underlying causes. The quality system itself must be formally audited at regular intervals to ascertain whether it is working as intended. We expect that all investigators joining the TARGIT trial will be working to local or national standards which conform to the international guidelines. The steering committee therefore is content that no additional quality assurance exercise is necessary for conventional external beam radiotherapy provided that the investigators at each site are subject to local/national guidelines similar to those quoted above. If no such scheme operates at an investigator site the principle investigator must inform the TARGIT Operations Office who will inform the International Steering Committee to determine an appropriate course of action.

